## Abstract

**Background:**

Excision of the pit of the sinus with phenolisation of the sinus tract and surgical excision are two treatment modalities for patients with sacrococcygeal pilonidal sinus disease. Phenolisation seems to have advantages over local sinus excision as it is performed under local anaesthesia with a relatively small surgical procedure, less postoperative pain, minor risk of surgical site infection (8.7%), and only a few days being unable to perform normal activity (mean of 2.3 days). The disadvantage may be the higher risk of recurrence (13%) and the necessity to perform a second phenolisation in a subgroup of patients. Wide surgical excision of sacrococcygeal pilonidal sinus disease has a recurrence rate of 4 to 11%. The disadvantages, however, are postoperative pain, high risk of surgical site infection, and a longer period being unable to perform normal activity (mean of 10 days). The objective of this study is to show that excision of the pit of the sinus of sacrococcygeal pilonidal sinus disease with phenolisation of the sinus tract is a successful first-time treatment modality for sacrococcygeal pilonidal sinus disease accompanied by a quicker return to normal daily activity compared to local excision of the sinus.

**Methods/design:**

Patients with sacrococcygeal pilonidal sinus disease will be randomly allocated to excision of the pit of the sinus followed by phenol applications of the sinus tract or radical surgical excision of the sinus. Patients are recruited from a single Dutch teaching, non-university hospital. The primary endpoint is loss of days of normal activity/working days. Secondary endpoints are anatomic recurrence rate, symptomatic recurrence rate, quality of life, surgical site infection, time to wound closure, symptoms related to treatment, pain, usage of pain medication and total treatment time. To demonstrate a reduction of return to normal activity from 7.5 days in the excision group to 4 days in the phenolisation group, with 80% power at 5% alpha, a total sample size of 100 is required.

**Discussion:**

This study is a randomised controlled trial to provide evidence that phenolisation of the sinus tract compared to radical excision reduces the total number of days unable to perform normal activity.

**Trial registration:**

Dutch trial register NTR4043, registered on 24 June 2013.

## Background

Sacrococcygeal pilonidal sinus disease (SPSD) is an acquired disorder of the natal cleft. In patients with SPSD, there are one or more sinus openings in the natal cleft with a blind-ending subcutaneous sinus. It has a prevalence of 8.3% [1]. There is a sex preponderance in men presenting with SPSD between the age of 20 and 30 years [2]. Although 3.7% of patients do not have any symptoms (silent disease), SPSD may cause symptoms interfering with quality of life and social function [1]. Symptoms associated with SPSD are pain, itch and discharge from the sinus with soiling of the underwear. Moreover, infection of the sinus with abscess formation may develop. In patients with silent SPSD, watchful waiting should be the treatment of choice [3]. An abscess requires simple surgical drainage. For patients with complaints due to chronic SPDS interfering with normal daily life, however, several treatment options have emerged in the past years. Simple excision of the pit of the sinus according to Lord and Miller [4], radical excision of the sinus and unroofing of the sinus are frequently used treatment modalities for SPSD [5].

Radical surgical excision of the sinus with primary wound closure or secondary wound healing is the most frequently used treatment for chronic SPDS [4,6,7]. Surgical site infection (SSI), however, is a frequent complication of radical excision with prevalence up to 24% [2]. SSI leads to secondary wound healing which may take several months to cure [8]. The use of a gentamicin-absorbed collagen sponge on the sacrococcygeal fascia reduced the infection rate after primary closure from 20% to 5% in one study [9], although this difference could not be confirmed by another study (26% versus 22%) [10]. The relatively big surgical trauma and the high rate of wound complications after radical excision results in a long wound healing time (mean (standard deviation (SD)) of 15 (4.9) days) and a long mean time to return to normal activity (9.7 (3.6) days) [2,5]. The recurrence rate after excision of SPSD is another problem. Midline wound closure after excision of SPSD has a mean (SD) recurrence rate of 11.1% (0.81%). Off-midline wound closure (Karydakis flap reconstruction), however, possibly seems to decrease the recurrence rate to 4% [2,5].

Another minimal invasive treatment modality for SPSD is excision of the pit(s) of the sinus followed by the applications of phenol into the sinus tract. Phenol has sclerosant properties destroying epithelium and debris in the sinus and is thereby able to promote healing of the sinus [11]. This procedure, first described in 1964, is performed in an ambulatory setting under local anaesthesia [12]. Other advantages of this treatment modality over radical surgical excision of SPSD are a smaller surgical wound with less pain and faster wound healing, and therefore faster recovery and return to normal activity. A disadvantage is the higher recurrence rate. A review of the literature in 2009 [13] reported a mean (SD) recurrence rate of 12.6% (0.91%) after follow-up of 2 years, but without results from randomised controlled trials. Therefore, some patients require another phenolisation treatment to cure the SPSD. The surgical site infection rate after phenolisation treatment was reported as 8.7%. The mean (SD) return to work after the procedure was within 2.3 (3.8) days [13]. Some other cohort studies have been performed since then showing a recurrence rate varying between 8.7 and 33.3% after a follow-up of 22 to 26 months. Mean wound closure time varied from 16 to 28 days, SSI from 0% to 8.7% and return to work from 0 to 3 days [11,14-16].

### Rationale

Excision of the pit of the sinus of SPSD with phenolisation of the sinus tract seems to have advantages over the most used surgical treatment for SPSD - radical sinus excision - as it is performed under local anaesthesia with a relatively small surgical procedure, less postoperative pain, minor risk of SSI (8.7%) and only a few days unable to perform normal activity (mean of 2.3 days). The disadvantage may be the higher risk of recurrence (up to 33%) and phenolisation may have to be repeated a second time. However, high-quality randomised controlled trials comparing both treatment modalities are importantly lacking.

### Objective

The primary objective of this randomised controlled trial is to show that phenolisation of the sinus tract is a successful treatment modality for SPSD and reduces the total number of days unable to perform normal activity.

## Methods/design

This study protocol was constructed according to the SPIRIT guidelines [17].

### Study design

This study is designed as a randomised, non-blinded, single centre, superiority trial with two parallel groups.

### Setting

Patients will be enrolled from a Dutch teaching, non-university hospital.

### Eligibility criteria

#### Inclusion criteria

To be eligible to participate in this study, a subject must meet all of the following criteria: 1) symptoms due to chronic SPSD interfering with daily life; 2) age ≥18 years; and 3) written informed consent is obtained.

#### Exclusion criteria

A potential subject who meets any of the following criteria will be excluded from participating in this study: 1) No or minimal symptoms related to SPSD; 2) suspicion of extensive subcutaneous network of sinus tracts; 3) abscess of SPSD; and 4) previous surgical procedures for SPSD.

### Interventions

#### Intervention: excision of the sinus pit and phenolisation of the sinus tract

Patients are treated in an outpatient setting, under local anaesthesia and aseptic conditions. The patient is positioned in the prone position on the proctology table. The operative area is shaved. No antibiotics are used. The skin is cleaned with an antiseptic solution and covered with a sterile dressing. Circumferential field block infiltration anaesthesia of the sinus is applied, using Lidocaine HCl 2%/epinephrine 1:100,000 (Pharmacist Hospital Haarlem, Haarlem, The Netherlands). Probing via the pit(s) of the sinus is performed to determine the direction of the sinus. Then, a very limited excision of all pits in the midline is made. Additionally, all out-of-midline openings are also excised as little as possible. A small sharp spoon is introduced via all separate orifices to curettage the sinus tract. Attention is paid that all hairs are removed from the sinus tract. After extensive curettage of the sinus tract, accurate haemostasis is reached by external compression. Gauze is used to protect the anus, and the surrounded skin is protected by a coating of vaseline (Pharmachemie BV, Haarlem, The Netherlands). Liquid phenol (85%; Meander Medical Centre, Amersfoort, The Netherlands) is injected by one or more 1 mL syringes (depending on the volume of the sinus tract) with a small catheter via one orifice until phenol is seen at the other orifices. This volume is accepted as the sinus tract volume. The phenol is left in place for 1 minute and aspirated afterwards. This procedure is repeated once. Afterwards, remaining phenol is washed out with ethanol (70%; Fresenius, Schelle, Belgium) to neutralise the phenol. The surrounding skin is cleaned with normal saline. The wound is covered with an absorbing bandage only to prevent soiling of the clothes. The patient is discharged immediately after the procedure.

#### Comparison: radical surgical excision

Patients are treated in a 1-day surgery setting under spinal or general anaesthesia, depending on the preference of the patient or anaesthesiologist. The patient is positioned in the prone position on the operating table. The buttocks are separated with plasters optimising the view of the area of the natal cleft. The operative area is shaved. No antibiotics are used. The skin is cleaned with an antiseptic solution and covered with a sterile dressing. Probing via the pit(s) of the sinus is performed to determine the direction of the sinus. Then, a limited asymmetrical incision of the skin around the sinus is made with the diathermia. An asymmetrical skin incision is preferred to be able to close the wound off-midline. All off- and midline orifices are included in the excision of the sinus. Subsequently, the sinus is radically excised with the diathermia. The subcutaneous tissue is mobilised to be able to close the wound off-midline. Haemostasis is reached by electrocautery. After complete haemostasis, the plasters are loosened to remove the tension on the wound in the natal cleft. A gentamicin-absorbed collagen sponge (Garacol 130 mg sponge; EUSA Pharma (Europe) Ltd, Oxford Science Park, Oxford, UK) is partitioned into numerous small parts and positioned on the sacrococcygeal fascia. Subsequently, the wound is closed off-midline with several separate hand-tied absorbable sutures. The edges of the wound are infiltrated with Lidocaine HCl 2%/epinephrine 1:100,000 (Pharmacist Hospital Haarlem, Haarlem, The Netherlands) for postoperative pain reduction. The skin is closed with separate non-absorbable vertical mattress sutures. The patient is discharged the same day.

### Outcomes

#### Primary endpoint

The primary endpoint is the loss of days of normal activity, measured from the day of operation. Patients do not have any restrictions after the surgical intervention. Complaints due to the intervention are the only factors restricting patients from performing their normal activities. Return to normal activity, such as working or doing housekeeping work, is assessed by filling in a diary during the first 2 weeks after surgery by all participants. As this study mainly includes young and active patients, this outcome measure is highly relevant.

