### Participant timeline

Patients who meet the inclusion criteria will be randomly assigned to either group A (pit excision followed by phenolisation) or group B (primary surgical excision). Patients randomised to group A are treated with excision of the sinus pit and phenolisation of the sinus tract. Afterwards, patients enter into the follow-up programme. If there is recurrent anatomic SPSD combined with symptoms interfering with daily life after at least 6 weeks, the phenolisation procedure is repeated. The treatment in group A can therefore consist of up to two phenolisation sessions. Patients randomised to group B primarily undergo excision of the sinus. Afterward, patients enter into the follow-up programme.

Data regarding quality of life and complaints related to SPSD are obtained preoperatively by questionnaires. Furthermore, the number and locations of pits of the SPSD in the natal cleft are preoperatively assessed. After the procedure, patients enter the follow-up programme. This consists of a diary during the first 2 weeks after the intervention to score complaints related to the surgical intervention, usage of pain medication and loss of days to perform normal activity and, at 1, 2, 6, 12, 26 and 52 weeks after the surgical intervention, quality of life scores, complaints in the natal cleft, satisfaction assessment and wound assessment are measured.

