### Data collection

Preoperatively, complaints related to SPSD (discharge, pain and itch) are evaluated and each symptom is scored by the participants on a six-point scale from 0 (no complaints) to 5 (daily complaints). Quality of life is also preoperatively measured, both by a visual analogue scale (scored from 0 (worst) to 100 (best)) and the Short Form (SF)-36 [19]. The SF-36 is a questionnaire designed to measure health-related quality of life. This questionnaire consists of 36 questions comprising eight different domains of quality of life: physical functioning, physical role limitation, emotional role limitation, bodily pain, vitality, mental health, social functioning, and general health. For each domain, a score between 0 and 100 can be obtained; the higher the score, the better the quality of life.

During the phenolisation procedure, the following items are assessed with an assessment form: number of pit excisions in midline and right and left from the midline and volume of phenol administrated in the sinus. For the excision procedure, the size and depth of the wound is measured as well as the weight of the excision specimen. For both procedures, duration of operation and possible complications are recorded.

A diary is obtained for the first 2 weeks after the intervention to score complaints related to the treatment (fluid, pain, irritation, itch, burning), scored on a six-point scale from 0 (no complaints) to 5 (daily complaints). Additionally, pain is evaluated with a visual analogue scale, scored from 0 (no pain) to 100 (extreme painful), usage of pain medication (yes or no) and if the patient is able to perform normal activity such as working or doing housekeeping work.

The postoperative questionnaire assesses the following items: patient satisfaction by the Visick satisfaction rate (disease scored by the patient as cured, improved, unchanged or worsened; the last two are considered as symptomatic recurrence) [18], symptoms related to the treatment (fluid, pain, irritation, itch, burning; scored from 0 (no complaints) to 5 (daily complaints), and quality of life as obtained by both a visual analogue scale and the SF-36 (both are assessed as described for the preoperative stage).

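### The primary endpoint attributes every lost day to the intervention in patients already limited by their disease, and the planned t test leaves the preoperative role-limitation score unused (minor)

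*Protocol article*

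**What the plan says.** All references are to the protocol article.

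- **Primary endpoint:** "The primary endpoint is the loss of days of normal activity, measured from the day of operation". Two sentences of explanation follow: "Patients do not have any restrictions after the surgical intervention", and then "Complaints due to the intervention are the only factors restricting patients from performing their normal activities".
- **Inclusion criteria:** a patient must have "symptoms due to chronic SPSD interfering with daily life". **Exclusion criteria** remove those with "No or minimal symptoms related to SPSD".
- **Data collection:** the two-week postoperative diary records "if the patient is able to perform normal activity such as working or doing housekeeping work". No question about the cause of a lost day is described.
- **Participant timeline** and **Data collection**, before surgery: "Data regarding quality of life and complaints related to SPSD are obtained preoperatively by questionnaires". These are symptom scores ("Preoperatively, complaints related to SPSD (discharge, pain and itch) are evaluated"), a quality-of-life visual analogue scale and the SF-36, whose domains include physical functioning, physical role limitation and social functioning. The diary's activity item is not described as taken at this stage.
- **Statistical methods:** continuous outcomes are compared between arms with an independent-samples t test. No baseline adjustment is mentioned.

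**The concern.** The eligibility criteria select people whose daily life is already disturbed by the disease. The endpoint section then treats the intervention as the sole source of restriction. Nothing in the article supports that for this population, and the described data cannot test it directly, because the activity item has no preoperative counterpart.

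The symptom scores do not separate the causes either. Pain and itch are scored before surgery as complaints of the disease and after surgery as complaints of the treatment.

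Two things are at stake. First, a patient who could not do usual activities before surgery may go on losing days for the same reason. Those days enter the primary count as variation unrelated to treatment, or take up diary days on which a treatment effect could have shown. Second, a report that patients lost a given number of days because of phenolisation, or because of excision, would claim more than the data show.

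**Working it through.** **1. The plan's own figure.** The Sample size section gives 7.5 versus 4 days (difference 3.5), two-sided alpha 0.05, 80% power and 50 per group. It cites literature SDs of 3.6 and 3.8 but does not say which SD was used.

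- Pooled SD = sqrt((3.6² + 3.8²)/2) = 3.70.
- n per arm = 2 × (1.96 + 0.84)² × SD²/3.5² gives 17, 18 and 19 for SDs of 3.6, 3.70 and 3.8. None gives 50.
- Solving for the SD at n = 50: 3.5 × sqrt(50/2)/(1.96 + 0.84) ≈ 6.25 days.

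Why 50 is not reproduced is a separate matter. Here it only means that both SDs, 3.70 and 6.25, have to be carried forward.

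**2. Is the comparison biased?** Allocation is random, 1:1, so pre-existing restriction is balanced in expectation. As a check, 20,000 null trials of 50 per arm were simulated for each assumed share p. Days lost were drawn around 6 with SD 3.70, limited to 0–14, and a share p of patients in both arms was set to 14 days. For p = 0, 0.10, 0.20 and 0.30 the mean arm difference stayed within 0.01 day of zero and the type I error was 0.048 to 0.052. There is no bias under the null.

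**3. What could it cost in power?** The article gives no share of patients restricted before surgery, so p is an assumption. In this deliberately heavy model, a share p in both arms loses all 14 days regardless of treatment:

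- difference = (1 − p) × 3.5
- variance in an arm with mean m = (1 − p) × SD² + p(1 − p)(14 − m)², averaged over m = 7.5 and m = 4
- power = Φ(difference/(SD_new × sqrt(2/50)) − 1.96)

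Worked line, p = 0.10 and SD 6.25 (unrounded 6.246):

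- Excision: 35.12 + 0.09 × 42.25 = 38.92.
- Phenolisation: 35.12 + 0.09 × 100 = 44.12.
- Mean 41.52, so SD_new = 6.44.
- Power = Φ(3.15/1.288 − 1.96) = Φ(0.485) = 0.69.

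| p (assumed) | Difference | SD_new from 6.25 | Power | SD_new from 3.70 | Power |
|---|---|---|---|---|---|
| 0 | 3.50 | 6.25 | 0.80 | 3.70 | 0.997 |
| 0.10 | 3.15 | 6.44 | 0.69 | 4.33 | 0.95 |
| 0.20 | 2.80 | 6.53 | 0.57 | 4.73 | 0.84 |

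**4. What could adjustment recover?** If the preoperative score correlates r with days lost within arms, linear adjustment multiplies the residual variance by about 1 − r². For assumed r of 0.1, 0.3 and 0.5 the reduction is 1%, 9% and 25%. That is like having 50/(1 − r²) = 50.5, 54.9 or 66.7 patients per arm in place of 50. The article gives no basis for choosing r.

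**The case against.** **The sentence is not a counting rule.** Read with the sentence before it, it most naturally means that the clinic imposes no rest period. The Objective, Data collection and Discussion sections all describe days on which normal activity was not possible, with no step that sorts days by cause. This stands. The wording is loose, but no rule for dropping days exists.

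**Symptoms that interfere with daily life need not stop someone working or doing housework.** This also stands. The two statements are in tension; they are not logically incompatible. The share of patients truly restricted may be small.

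**A reader might infer a bias towards phenolisation:** that days lost to lingering disease would be discounted in that arm only, because excision removes the sinus at once. The document does not support this.

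- It would need a step that attributes each day to a cause, and none is described.
- The phenolisation closure times of 16 to 28 days in the Background do not establish an asymmetry. The same section gives a mean of 15 days for wound healing after radical excision, which also passes the 14-day diary. Closure time is in any case not a measure of persisting disease.
- Under an all-days count, any lingering disease is charged to phenolisation, which works against the trial's hypothesis.

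**A reader might also infer that no preoperative information on activity exists.** That goes too far, since the SF-36 is taken before surgery and covers physical role limitation.

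**The power figures may count some variation twice.** The cited SDs come from treated patients with this disease and may already contain background restriction. This is fair, and the table should be read as an illustration.

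**Conclusion.** The point holds as a minor matter of precision and interpretation. The statement that only the intervention restricts activity is unsupported for patients selected because their disease interferes with daily life, and the article describes no baseline on the diary's own scale. The randomised difference in total days lost is not biased by this. The costs are noise or dilution of unknown size and per-arm counts that cannot be attributed wholly to treatment.

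Under the heavy assumption above, a 10% to 20% share takes power from 0.80 to 0.69–0.57 at an SD of 6.25, but only from 0.997 to 0.95–0.84 at an SD of 3.70. Both the share and the working SD are unknown, so neither range is a finding about this trial.

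**What to change.** 1. In the Primary endpoint section, replace the attributing sentence with a statement that the primary count is all diary days on which normal activity was not possible, whatever the cause. This agrees with the Objective, Data collection and Discussion sections. On its own it changes no result, but it settles how the count is read.
2. In Statistical methods, make the primary comparison a linear model with treatment arm and the preoperative SF-36 physical role limitation score, in all randomised patients. Keep the unadjusted t test as a sensitivity analysis. Because allocation is by simple randomisation, adjustment also guards against chance imbalance in this score.
3. Report days per arm as days lost after each procedure, not as days caused by it.

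The cost is one covariate to pre-specify and one sentence to rewrite. The score is already part of the preoperative assessment, so the 40 patients included at the time of the article are covered and no new item is needed. The gain in precision depends on an unknown correlation and may be small.
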